**Fig 3. Study Design and Procedure**

*The upper portion of the figure illustrates the overall study design. The middle portion depicts the timeline for assessing scales and EEG at baseline, post-intervention, and follow-up timepoints. Brief mindfulness and relaxation training will be administered to both the intervention and control groups after recruitment. The baseline assessment (-T1, T0) will be completed before the intervention. Audio guidance will be provided for daily practice in the BMT group, while there will be no additional practice or intervention for the control group after training. The lower portion of the figure represents the modules of psychological and behavioural assessments during the baseline and five follow-up sessions. The cue-reactivity task will be implemented using a customized two-choice oddball paradigm. INT: intervention, rs-EEG: resting-state EEG; BMT: brief mindfulness training; VAS: Visual analogue scale; SMT: state-mindfulness.*

1. ***Sample size estimation. [List the four elements: δ(Δ) or π1, π2, α, β or Power, and provide the calculation formula]***

In this study, the subjective reports of smoking urges (QSU-Brief) will be used as the primary outcome measure. Referring to study of similar populations **^[28]^**, We set δ(Δ)_tot_ = 4 to represent the anticipated reduction of 4 points in the QSU-Brief score after the intervention in the experimental group. Multiple measurements of the QSU-Brief will be conducted on participants before and after the training, as well as during the 60-minute online training period. To estimate Cohens’d, we have set α = 0.05 and β = 0.80. Cohens’d can be calculated using the formula Cohens’d=(δ(Δ)/SD_estimate_), where the estimated SD_estimate_ was 7.65 based on reference study. Therefore, the corresponding command is pwr.t.test (d=cohens_d, sig.level = 0.05, power = 0.80, type = "paired", alternative = "two.sided"), and the estimated sample size is 34. Therefore, the minimum required sample size for the experimental group is 34. Considering a natural dropout rate of 30%, the sample size for the experimental group should be no less than 45.

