1. ***Blinding. [Blinding is used in treatment studies and diagnostic trials to reduce the risk of implementation bias and measurement bias. Implementing strict confidentiality measures, such as using placebos or simulating procedures, is an effective blinding method. If blinding is necessary and feasible for your study, describe the methods and procedures for implementing blinding]***

This trial includes group therapy sessions for students from the same school. As a result, participants may already know each other or be unfamiliar with one another, and they may naturally discuss the experimental training they receive. Maintaining blinding for the researchers is challenging as they may be influenced by the experimental content during the trial. Therefore, meeting the requirements of double-blinding in a clinical trial is not feasible in this situation

1. ***Outcome Measures. [Outcome measures are used to evaluate the results of a study and can include primary, secondary, and safety measures, including adverse events and reactions. Please describe the names of the measures, the methods of measurement, and the time points at which they are assessed]***

As listed in **Table 1**, the primary outcomes include subjective reports of smoking craving, changes in EEG indicators, and mindfulness measures (both trait- and state- mindfulness). The secondary outcomes will be daily smoking behaviours (number of cigarettes smoked per day, exhaled carbon monoxide concentration), affect and impulsivity, as well as indicators reflecting correlation between mindfulness and smoking cue-reactivity. Researchers will inquire daily during the intervention period whether participants experience tobacco withdrawal symptoms or any other adverse reactions. Participants are also encouraged to proactively contact the research team if they experience any adverse reactions. Please refer to item 9 for the time points of assessment.

| **Table 1. Evaluated variables** | | | |
| --- | --- | --- | --- |
| **Variables** | **Timepoints** | **Measures** | **Outcome level** |
| **Category 1: smoking related indices** | | | |
| **Nicotine dependence** | -T1, T0, T1-T5 | **Fagerstrőm test for nicotine dependence (FTND)** is a six-item revision of the Fagerstrőm Tolerance Questionnaire **^[31]^**，scored as 0-3 (low), 4-6 (moderate), and 7-10 (high) with the summed score **^[32]^**. | primary |

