| **Craving** | -T1, T0, T1-T5 | **1.Tobacco Craving Questionnaire-Short Form (TCQ-SF**）is short form of 12 optimized projects to assess smoking craving levels，including four factors of emotionality, expectancy, compulsivity, and purposefulness **^[33]^**, with each factor scores from 3 to 21 points, was used in Chinese population**^[34]^**. | primary |
|  |  | **2.Questionnaire on Smoking Urges-Brief（QSU-Brief）**developed by Cox et al., **^[35]^** suitable for multiple measurements in laboratory and clinical use, including 10 items, can be completed in less than 2 minutes. Each item uses a subjective score of 1-7 points to evaluate the current level of craving for tobacco, the Chinese version will be adopted **^[36]^**. |  |
| **VAS for craving** | -T1, T0, T1-T5, during CR task | **Visual analogue scale (VAS)** administered during cue-reactivity experiment to measure the state of craving, responses to each item were rated using a scale that ranged from 0 (not at all) to 10 (the strongest feeling possible). | primary |
| **Number of cigarettes smoked per day** | -T1, T0, T1-T5 | Self-report for number of cigarettes smoked per day. | secondary |
| **Exhaled carbon monoxide (CO)** | T0, T1-T5 | Instantaneous reading device (Bedfont piCO Smokerlyzer) used to identify whether the duration of cigarette cessation meets the requirements. | secondary |
| **Category 2: mindfulness** | | | |
| **Trait-mindfulness** | T0, T1-T5 | **Five Facet Mindfulness Questionnaire（FFMQ）**consisting of 39 items and 5 factors, namely observation, description, acting with awareness, non-reactivity, and non-judging, the Chinese version will be used**^[37]^**. | primary |
| **State-mindfulness** | T0, T1-T5, during CR task | Based on the Toronto Mindfulness Scale (TMS), two items in Chinese version **^[38]^** were used to evaluate the dimensions of curiosity and decentralization. | primary |
| **Category 3: brain function** | | | |
| **Brain function** | T0, T1-T5 | Using a 64-channel EEG system to record in both resting and experimental conditions. | primary |
| **Category 4: Socio-demographic and clinical information** | | | |
| **Self-emotional assessment** | T0, T1 | **Self-assessment manikin (SAM)** used to measure the emotional state during 7-day mindfulness intervention. | others |

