All data will be analyzed upon completion of data collection. The data analysis process will strictly adhere to the principles of the blind method. Analysis of the data will be conducted using R software (https://www.r-project.org/), IBM SPSS Statistics for Windows, V20.0 (SPSS), MATLAB (MathWorks in Natick, Massachusetts, USA), and EEGlab (https://sccn.ucsd.edu/eeglab). Descriptive statistics will be used for demographic, psychological, and behavioural data at baseline. Two-sample t-tests and χ^2^ tests will be performed for continuous and categorical variables between the intervention group and control group. Repeated measures MANOVA will be adopted to examine intervention effects while adjusting for individual factors and pre-intervention variables (e.g., trait mindfulness and smoking indices). Within-group effects will be investigated through serial trend analysis from -T1 to T5. Linear mixed-effects model analysis will include data from all measures at different timepoints to explore factors associated with smoking cue-reactivity for both groups. EEG data will be preprocessed using Matlab software and the EEGLab toolbox. Relative spectrum power for six EEG bands (delta: 1-4Hz, theta: 4-8Hz, alpha: 8-13Hz, low-beta: 13-20Hz, high-beta: 20-30Hz, and low-gamma: 30-48Hz) will be calculated at the single electrode and ROI level. Microstate and phase synchronization analysis will be conducted, and source localization analysis will be used to investigate functional changes in subcortical brain regions. Repeated measures analysis of variance and simple effect analysis will be performed for EEG indices, considering significance in the professional field. Effect size will be measured using Cohen's d or partial eta-squared values **^[46]^**.

1. ***Participant management system.***

(1) **Contact and Guidance:** A contact group consisting of relevant researchers is responsible for providing guidance and addressing any study-related questions for participants throughout the entire study period. This ensures that participants have a clear understanding of the study and can actively cooperate with the research process. Researchers are required to respond promptly and keep records for participants who withdraw, are excluded, lost to follow-up, terminated, or suspended.

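### The protocol defines its primary outcome in three conflicting ways: QSU-Brief alone for the sample size, three outcome families in the text, and six rows (seven instruments) in Table 1

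*Protocol*

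**What the plan says.** Three places in the Protocol define the primary outcome.

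- **Sample size estimation.** The wording is singular: "the subjective reports of smoking urges (QSU-Brief) will be used as the primary outcome measure". The calculation uses a 4-point fall in the experimental group, SD 7.65, two-sided alpha 0.05, power 0.80 and a paired t-test. It gives 34, raised to 45 for dropout.
- **Outcome Measures, text.** Here "the primary outcomes include subjective reports of smoking craving, changes in EEG indicators, and mindfulness measures", the last covering both trait and state mindfulness.
- **Outcome Measures, Table 1.** Six rows carry the level primary: nicotine dependence (FTND), craving, VAS for craving, trait mindfulness (FFMQ), state mindfulness and brain function (64-channel EEG). The craving row holds two instruments, "1.Tobacco Craving Questionnaire-Short Form (TCQ-SF" and "2.Questionnaire on Smoking Urges-Brief". The level cell beside the second is blank and is read here as continuing the row. That makes seven instruments, each assessed at T1 to T5.

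The text introduces its list as being the one in Table 1, but FTND, a dependence score "scored as 0-3 (low), 4-6 (moderate), and 7-10 (high) with the summed score", is primary only in the table.

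The study design section sets the aim as superiority over control in reducing craving. It does not say which measure, or which visit, must show it.

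**The concern.** Naming the primary outcome is the protocol's own task, and here three readers could come away with three answers: one questionnaire, three families, or seven instruments. EEG is the least defined, because it is labelled primary without any index being chosen from among the band powers, microstates, phase synchronization and source estimates in the analysis section.

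Two things are at stake. First, the superiority claim has no fixed target, so the measure and visit that carry the headline could be settled after the data are seen. Second, the mindfulness scales measure what the intervention trains. The control arm receives relaxation, and the Blinding section says that double-blinding is not feasible. A higher self-reported mindfulness score in the trained arm could count as a primary success with craving unchanged, although craving is the stated aim.

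**Working it through.** **1. The definitions side by side**

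| Measure | Sample size section | Outcome text | Table 1 |
| --- | --- | --- | --- |
| QSU-Brief | primary, sole | primary (craving) | primary (craving row) |
| TCQ-SF, craving VAS | not named | primary (craving) | primary |
| FFMQ, state mindfulness | not named | primary | primary |
| EEG | not named | primary, no index | primary, no index |
| FTND | not named | not listed | primary |

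QSU-Brief is the only measure that the singular wording allows. The places differ on everything else. None names a primary visit.

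**2. What the sample size covers**

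Inputs from the sample-size section: difference 4, SD 7.65, two-sided alpha 0.05, power 0.80, paired test.

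- d = 4 / 7.65 = 0.523.
- The paired t-test then needs 30.7, so 31. The stated 34 is not reproduced with this d. Rounding d to 0.5 gives 33.4, so 34, which is the likely source.
- 34 × 1.3 = 44.2, so 45, as stated. Dividing by the retained fraction instead gives 34 / 0.7 = 48.6, so 49.

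The calculation covers one measure, one arm and one before-after change. It names no visit.

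**3. Chance of a false positive if any one primary measure suffices**

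Assumptions, not in the Protocol: each measure is tested once at one visit at 0.05, and any significant result counts as success.

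- Seven independent tests: 1 − 0.95^7 = 0.302.
- Six tests, counting the labelled rows: 1 − 0.95^6 = 0.265.
- Seven equally correlated normal test statistics, simulated, counting |Z| > 1.96:

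| Common correlation (assumed) | 0 | 0.3 | 0.5 | 0.7 | 0.9 |
| --- | --- | --- | --- | --- | --- |
| At least one false positive | 30% | 27% | 23% | 18% | 11% |

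Every case exceeds 5%. With one primary measure at one visit, the rate is 5% by construction.

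**4. Keeping all seven under a Bonferroni rule**

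Alpha per test is 0.05 / 7 = 0.00714. The Protocol's paired formula then needs 49.3, so 50, against 31 unadjusted and 34 stated.

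**5. Power for a between-arm contrast in QSU-Brief**

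Assumptions: difference 4, SD 7.65 applies to change scores, no change in controls, equal arms (the sample-size section sizes only the experimental group), two-sided 0.05, two-sample t-test.

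| Analysed per arm | 31 | 34 | 45 |
| --- | --- | --- | --- |
| Power | 53% | 57% | 69% |

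A power of 80% needs 58.4, so 59 per arm. If 45 are enrolled and 30% drop out, 45 × 0.7 = 31.5 remain, so the 69% holds only if all 45 are analysed.

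**The case against.** The best defence is that the conflict is narrow. QSU-Brief is primary in all three places, and sizing a trial on one of several primary outcomes is not in itself an error. That is true, but it does not rescue the singular wording, the FTND mismatch or the undefined EEG endpoint.

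Several stronger readings are tempting and are not supported:

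- **Every primary measure is tested at 0.05 without adjustment.** The only alpha in the Protocol belongs to the sample-size calculation. An adjustment rule is commonly left to the statistical analysis plan, which is not at hand, so its absence here is no finding.
- **A chance finding would make the trial positive.** No success rule is stated. If all primary measures had to succeed, there would be no inflation, though power would fall.
- **Seven measures at five visits mean 35 tests.** The analysis section plans repeated measures MANOVA, repeated measures ANOVA for EEG, and mixed models over all visits, not a separate test per visit. It does not say that the MANOVA gates later tests, so protection is not shown either.
- **EEG means 64 × 6 = 384 uncorrected tests.** The text says that band power "will be calculated at the single electrode and ROI level", which describes how features are derived. The stated inference is repeated measures ANOVA with simple effects.

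A further fair point is that EEG belongs to the stated objective, so it should not be reduced to a mere exploratory outcome.

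**Conclusion.** The concern holds as a contradiction within the Protocol over which outcome is primary, with no primary visit and no EEG index fixed. This does not depend on the unseen analysis plan, which could add an adjustment but could not make the three places agree.

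The 18 to 30% range indicates what the ambiguity permits. It rests on an any-positive rule, one visit, tests at 0.05 and assumed correlations of 0.7 down to 0. It is not an error rate of the planned analysis. The power figures of 57% and 69% rest on the assumptions in step 5 of the working, chiefly that 7.65 is the SD of change and that controls do not change.

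It should be settled before enrolment. The Protocol says that the trial has not begun, and a choice made after seeing data would weaken the superiority claim.

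**What to change.** Make the sample-size section, the outcome text and Table 1 agree:

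1. **Primary:** the between-arm difference in QSU-Brief post-intervention (T1). This matches the stated aim of superiority over control in reducing craving.
2. **Secondary:** FTND, TCQ-SF, craving VAS, FFMQ, state mindfulness, and QSU-Brief at T2 to T5.
3. **Key secondary or mechanistic:** EEG, with the indices named and correction over electrodes and bands.
4. **Sample size:** state that the present calculation is for a within-group paired change in the experimental arm and does not cover this contrast. Restate the power or the sample size for the between-arm comparison, and give the control-group size.

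The relabelling costs only wording and changes no data collection. Fewer measures can then carry the headline claim. Restating power may show that more participants are needed: under the assumptions above, 59 analysed per arm for 80% power. If the investigators prefer several primary measures, they must state the success rule and size the trial for it.

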To examine the effectiveness of brief mindfulness intervention in reducing smoking cravings, this study employs a randomized controlled parallel trial design. Expanding upon existing literature that supports the positive effects of brief mindfulness interventions, the primary aim of this study is to establish the superiority of brief mindfulness intervention over the control group within the intervention conditions. The trial consists of four distinct stages: participant recruitment, baseline measurement, measurement during the intervention period, and follow-up measurement. After the completion of each stage, pertinent evaluations will be conducted to assess the outcomes. The design flowchart, depicted in **Fig 3.**, illustrates the methodology employed in this study. It is important to note that the trial has not yet begun, and it is expected that the entire process, including participant recruitment, data analysis, and article writing, will take approximately one year. Additionally, a follow-up period of one year will be conducted to assess the long-term effects of the intervention.

**
[figure not shown]
**

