1. ***Methods of randomization and concealed allocation. [Randomization is used to reduce the risk of selection bias. Methods for generating random number sequences include computer software, random number tables, semi-random or pseudo-random methods (such as using dates, birthdays, or even/odd numbers of hospital visits). Please describe the individuals involved in generating random number sequences and the methods they use. Concealed allocation is used in treatment studies to reduce the risk of selection bias. Key steps in concealed allocation include having a designated person determine the allocation sequence, ensuring that this person is not involved in enrolling participants, and securely storing the allocation table. Please provide detailed descriptions of these steps. Central randomization is a robust method of concealed allocation. Describe the individuals and methods involved in determining the allocation sequence]***

(1) In this study, the intervention period for the BMT, which is a behavioural training, lasts for one week. Baseline data, including EEG data, will be collected from all participants. Following this, there will be a one-week training period for the intervention content, after which post-intervention data, including scales, self-reports, and EEG data, will be collected. Follow-up measurements will be conducted at 1 week, 1 month, 3 months, 6 months, and 1 year after the trial's completion. Group allocation will be performed after the completion of baseline data collection.

(2) The primary intervention method employed in this study is the brief mindfulness-based intervention of "STOP" **^[29, 30]^**, with a 7-day ~60-min sessions mindfulness course for the experimental group. Meanwhile, the control group will undergo relaxation training. All recruited participants are from the same school, and due to the lack of blinding execution conditions, achieving double-blind standards may present challenges.

(3) The randomization process for this trial will involve the use of a random sequence generator website (https://www.random.org/). This website will be utilized to ensure the random assignment of participants to either the experimental or control group.

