| **Anxiety** | -T1 | **Generalized Anxiety Disorder (GAD-7)** used to measure anxiety related problems over the past two weeks, with each project scoring 0-3 points and a total score of 0-21 points **^[25]^**, with scores of 5, 10, and 15 corresponding to the cutoff values for "mild", "moderate", and "severe" anxiety levels **^[45]^**. | others |

*CR: cue-reactivity.

1. ***Definition of Participant Effectiveness Determination. [This includes definitions for participant withdrawal, exclusion, loss to follow-up, confounding factors, study discontinuation, and study suspension]***

(1) **Participant Withdrawal:** Each participant has the right to withdraw from the study at any time without the need to provide a reason. Participants who choose to withdraw voluntarily will not be included in the analysis. As part of our comprehensive research procedure, we have established a protocol for managing participants who decide to withdraw. If participants are willing to provide a reason for their withdrawal, it will be documented and recorded.

(2) **Participant Exclusion:** Due to the inability to ensure full intervention participation in the intervention group during the training process, the "STOP" training period lasts for one week. Participants who have participated in less than 5 training sessions will be considered as not having received the complete intervention and, theoretically, should be excluded or adjusted using mixed effects models.

(3) **Participant Loss to Follow-up:** If a participant cannot be contacted for two consecutive visits after the completion of the intervention for any reason, they will be classified as lost to follow-up.

(4) **Participant Contamination:** Following the completion of the intervention, a survey will be conducted with the participants. If the control group attempts to learn about the training mode used by the intervention group (or vice versa) and attempts to replicate the training, they will be classified as contaminated participants.

(5) **Participant Termination:** To prioritize participant health, any adverse events (including tobacco withdrawal symptoms) will be considered termination criteria. Researchers will discuss with the participant who experiencing such conditions and terminate the intervention early. Participants will receive appropriate clinical interventions only with their explicit consent.

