(6) **Participant Suspension:** Participants in this study can request to suspend the intervention. If a suspension is requested, the participant will be evaluated by the study team and, if approved, moved to the future intervention group. Data collected before the suspension will not be included in the final data analysis.

1. ***Definition, identification methods, and management systems for adverse events and reactions.***

In the "Chinese Clinical Smoking Cessation Guidelines," it is stated that smokers may experience a range of withdrawal symptoms after quitting or reducing smoking. These symptoms include smoking cravings, anxiety, depression, restlessness, headache, increased salivary gland secretion, lack of concentration, and sleep disorders. Withdrawal symptoms typically begin within hours of smoking cessation, peak within the first 14 days, and gradually diminish until they disappear. Most withdrawal symptoms last for about one month, although some patients may experience cravings for smoking for over a year.

**Definition:** Adverse events refer to any unfavorable or unintended signs, symptoms, or diseases that occur during or after the intervention, regardless of whether they are related to the intervention. Adverse reactions specifically refer to unfavorable or unintended responses that are causally related to the intervention.

**Identification Methods:** Adverse events and adverse reactions can be identified through various methods, including participant self-reporting, researcher observations, physical examinations, laboratory tests, and medical records.

**Management System:** In light of the potential adverse reactions mentioned above, the researchers will conduct daily inquiries during the intervention to determine whether participants have experienced any of the symptom. The delivered list will also provide information to participants, instructing them to promptly contact the researchers if they experience similar symptoms at any other time. In the event of any adverse reactions, responsible personnel from the medical school and psychology department will promptly contact the participants and assess their psychological and physiological conditions. Based on the participant's willingness, a collective decision will be made by the medical school, psychology department, and participant regarding their continued participation in the subsequent research. The researchers will record the reasons for their decision.

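### Rules that drop withdrawers and discard suspended participants' data after randomisation, plus an open rule for low attenders, expose the superiority comparison to selection bias

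*Protocol*

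**What the plan says.** The section on study design states that "the primary aim of this study is to establish the superiority of brief mindfulness intervention over the control group". The randomisation section says "Group allocation will be performed after the completion of baseline data collection". Anything that happens during training or follow-up is therefore post-randomisation.

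The section Definition of Participant Effectiveness Determination then sets three rules that bear on the analysis:

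- **Rule (1), withdrawal:** "Participants who choose to withdraw voluntarily will not be included in the analysis". It is unconditional and covers either arm.
- **Rule (2), fewer than 5 sessions:** such participants "theoretically, should be excluded or adjusted using mixed effects models". The rule opens with "Due to the inability to ensure full intervention participation in the intervention group during the training process" and refers to the STOP training. No session threshold is given for relaxation.
- **Rule (6), suspension:** "Data collected before the suspension will not be included in the final data analysis". If the request is approved, the person is "moved to the future intervention group". The arm to which they were randomised is not mentioned.

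The template heading of the statistical methods section asks whether intention-to-treat was used and how it compares with per-protocol. The text beneath it names neither.

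**The concern.** A superiority claim rests on the two arms being comparable because they were formed by chance. Removing people, or their data, because of later events gives that up. Whether someone withdraws, pauses or stops attending may well depend on craving or on perceived lack of benefit.

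The protocol itself offers one such route. Rule (5) ends the intervention early for any adverse event, counting tobacco withdrawal symptoms, and the adverse-event section lists craving among those symptoms. A participant stopped early for craving could end up with fewer than 5 sessions and become excludable, and craving is a primary outcome.

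The open choice in rule (2) adds a second problem: the analysis set, or the model, could be settled after the data are seen. The Blinding section concedes that double-blinding is not feasible.

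**Working it through.** **Is there an as-randomised analysis elsewhere?** The statistical methods section assigns the test of intervention effects to repeated measures MANOVA. It adds that "Linear mixed-effects model analysis will include data from all measures at different timepoints", but the stated purpose of that model is to explore what is associated with cue-reactivity in both groups. It does not say that people removed under rules (1), (2) or (6) are kept. The withdrawal rule is worded for the analysis as a whole. So no stated analysis restores all participants as randomised.

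**Does the adjustment option in rule (2) solve it?** No. Attendance is measured after allocation and may be affected by the training itself, so conditioning on it does not recover the randomised comparison.

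**How large could the bias be?** The protocol gives no figure for this, so there is none to reproduce. The illustration covers the session rule only, in the case where exclusion is chosen and applied in the mindfulness arm alone.

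Inputs from Sample size estimation: planned reduction 4 points on QSU-Brief; SD 7.65, taken here as the SD of the change. Assumed, not in the documents: true effect zero; the lowest share p of attenders removed, p = 20–30%; correlation r between attendance and craving improvement, 0.2–0.4; both normally distributed.

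Bias = r × φ(z_p)/(1 − p) × 7.65, where z_p is the normal quantile for p.

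- p = 20%: φ/(1 − p) = 0.280/0.80 = 0.350
- p = 30%: φ/(1 − p) = 0.348/0.70 = 0.497

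| r | p = 20% | p = 30% |
| --- | --- | --- |
| 0.2 | 0.54 | 0.76 |
| 0.3 | 0.80 | 1.14 |
| 0.4 | 1.07 | 1.52 |

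The range is 0.54 to 1.52 points, or 0.54/4 = 13% to 1.52/4 = 38% of the planned 4 points.

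**Cross-check with a simpler model.** If a fraction f of the mindfulness arm is removed and those people do c points worse than those retained, the bias is f × c.

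- f = 10%, c = 2 gives 0.2 points.
- f = 30%, c = 4 gives 1.2 points.
- f = 30%, c = 7.65 (a full SD, an extreme case) gives 2.3 points.

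Simulated with no true effect and an assumed 45 per arm before removal, the two-sided type I error was about 0.05, 0.11 and 0.22 in these three cases. The first model corresponds to c between 0.76/0.30 = 2.5 and 1.07/0.20 = 5.4, inside this range.

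**What equal loss would do.** If both arms lost the same share by the same mechanism, the formula gives equal shifts and zero bias under no effect. The figures above therefore do not measure the withdrawal or suspension rules.

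**The case against.** Several stronger readings are tempting, and the text does not carry them.

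- **Low attenders are definitely removed.** A reader might infer this, but exclusion is one of two options in rule (2). What stands is that the choice is open and neither option keeps the randomised comparison.
- **All three rules act unequally between arms.** The withdrawal and suspension rules are worded for every participant, so any imbalance from them would be empirical. Only the session rule is tied to one arm. Even there, its operative sentence speaks of training sessions in general, and controls also receive training. One-arm use is the likelier reading, not the only one.
- **Suspended controls cross over to mindfulness.** The phrase about a future group could equally mean a later cohort of the same arm. The fair criticism is that the text does not say the allocated arm is kept.
- **30% of each arm, about 14 of 45, would be lost to these rules.** The sample size section gives 45 for the experimental group only and no control-arm size. Its 30% is natural dropout, not the share these rules would remove.

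It can also be said that the size calculation rests on assumed correlations and that its sign depends on poorer attenders doing worse. That is correct, and it is why the figures are illustrative.

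Finally, one might expect a statistical analysis plan to define the analysis sets. It could do so here only by contradicting sentences the protocol already contains. The objection that the protocol is merely silent therefore fails.

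**Conclusion.** The concern holds in this form: the protocol excludes withdrawers and discards suspended participants' earlier data after randomisation, leaves open whether low attenders are excluded or adjusted for, and names no analysis of all participants as randomised. The superiority comparison is open to selection bias, and the session rule could make it differ by arm.

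The conclusion is firm for the withdrawal rule, which is unambiguous. For the session rule, the possible size is about 0.5–1.5 points against the planned 4, conditional on no true effect, removal in the mindfulness arm only, and the assumed shares and correlations. No figure can be given for withdrawal or suspension from what the protocol states. The point does not depend on the sample size calculation. It should be corrected before the trial starts, because following the rules as written undermines the main comparison.

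**What to change.** Change only the analysis sentences in rules (1), (2) and (6). The right to withdraw stays as it is. Suggested wording: *All randomised participants are analysed in the arm to which they were allocated, using all data collected, including data obtained before withdrawal or suspension, unless the participant withdraws consent to use the data.*

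In addition:

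- Make attendance of at least 5 sessions a per-protocol sensitivity analysis only, defined in the same way for relaxation sessions in the control arm.
- Invite participants who stop training to complete the scheduled T1–T5 assessments.
- Reconcile the suspension wording about a future group with the randomised allocation, so that for analysis the person stays in the allocated arm. How suspended participants are managed is for the investigators.

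The cost is protocol wording, continued follow-up contacts with people who have stopped training, and possibly a smaller effect estimate. The study design section says the trial has not begun, so the change can be made before any data exist.
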